# 4 Steps To My Future (4STMF): protocol for a universal school-based pilot and feasibility study of a CBT-based psychoeducational intervention to support psychological well-being amongst young adolescents in the Western Cape, South Africa

**DOI:** 10.1186/s40814-022-01035-x

**Published:** 2022-05-05

**Keywords:** Anxiety, Depression, Prevention, Universal, School-based, Mental health, CBT-based, Psychoeducational intervention, Pilot, South Africa

## Abstract

**Background:**

Mental health problems often emerge during middle childhood and adolescence. In South Africa, and in the context of high rates of poverty, violence, and adversity, many children are at a considerable risk for developing mental health problems. Access to and costs of mental health services preclude treatment for most. There is evidence that universal school-based prevention programmes are effective in well-resourced settings. However, little is known about the feasibility and acceptability of such programmes in low- and middle-income countries (LMICs), including South Africa.

**Methods:**

This is a feasibility pilot study of 4 Steps To My Future (4STMF), a Cognitive Behaviour Therapy (CBT) school-based programme for young adolescents in the Western Cape, South Africa. This eight-session intervention will be delivered to children in grade 5 (aged 10–13 years approximately) attending two public government-run schools in the Western Cape, South Africa. We aim to enrol approximately 224 children in grade 5. We will randomise which school receives the intervention first and the other will be a delayed intervention group. We will train individuals with a post-graduate degree in psychology to facilitate the programme. We will collect demographic data on participants as well as data on primary (feasibility measures) and secondary outcomes (mental health and well-being measures). We will collect data at baseline, post-intervention, and at 1-month follow-up.

**Discussion:**

This pilot study will provide data on the acceptability and feasibility of delivering a universal school-based prevention programme in South African schools. The study will provide preliminary data to inform the design of a full-scale randomised controlled trial (RCT) of a universal school-based mental health programme aimed at preventing mental health problems.

**Trial registration:**

This trial is registered with the Pan African Clinical Trial Registry (https://pactr.samrc.ac.za/TrialDisplay.aspx?TrialID=10881) database, with unique identification number for the registry: PACTR202004803366609. Registered on 24 April 2020.

## Background 

Globally, at least 1 in 5 children and adolescents experience mental health problems, and this number is likely to be even higher in low- and middle-income countries (LMICs), like South Africa [1], where vulnerable populations face multiple adversities [2]. In South Africa, the prevalence of anxiety disorder symptoms amongst children and adolescents is reported to be high, ranging from 22 to 25.6% amongst 7–13 years old, in the Western Cape Province [3]. Normative data from a number of studies conducted within the same context over the past decade (for example Burkhardt et al., 2003 [4], 2012 [5]; Muris et al., 2006 [6], 2008 [7]) consistently confirmed higher fear and anxiety levels in South African children, compared to their western counterparts. Thus, even before the COVID-19 pandemic, children and adolescents in South Africa were already particularly at risk of developing mental health problems because they are exposed to multiple risk factors such as violence, child maltreatment, living in households affected by HIV/AIDS, and poverty [1, 8–10]. Furthermore, the COVID-19 pandemic is having a profound effect on all aspects of society, including mental health [11]. Whilst disease containment measures (DCMs) have been implemented to help reduce the spread of the virus, such measures have had several unintended adverse consequences for children and young people (CYP). For example, learning was disrupted and social and emotional support was reduced [12–14].

Finding appropriate, cost-effective, and efficient ways to intervene is a key priority, given the impact of mental health problems both short and long term. In the short term, we know anxiety and depression impact on daily functioning, disrupt educational attendance and attainment, affect social relationships and interfere with normative development [10, 15–18]. In the long term, untreated depression is associated with an increased risk of subsequent depression, interpersonal difficulties, and suicide in adulthood [19, 20].

There is convincing evidence, predominantly from high-income countries (HICs), that psychological treatments, including Cognitive Behaviour Therapy (CBT), are effective in treating anxiety and depression [21–25]. CBT-based programmes for CYP with anxiety have been widely used in individual and group-based contexts [26]. There is emerging evidence of the effectiveness of CBT-based approaches in these populations in LMICs [27–35]. Paradoxically, in these countries, there is also a lack of trained clinicians, particularly in the most deprived areas, where the vulnerability factors for developing mental health problems are highest [1, 9, 10]. This lack of trained clinicians has led to interest in mental health prevention programmes, but to date, preventive interventions undertaken in LMICs are unfortunately lacking. A recent systematic review conducted by our team of universal school-based mental health programmes in LMICs identified 12 studies conducted in 11 different LMICs with children aged 8–19 years of age [36]. Whilst five studies reported improvement in depression, and five studies reported improvement in anxiety, overall, there were limited data on the outcomes of the studies, and only four provided explicit examples of how the interventions were developed or adapted for the local context. Also, none of the studies was conducted in South Africa, and none of the studies involved parents or caregivers in a direct way.

Whilst nearly 90% of all children live in LMICs, only 10% of randomised trials are undertaken in these countries, with almost all being psychopharmacological trials [1]. This highlighted the need to develop and evaluate mental health prevention programmes for children in LMICs with schools providing a promising context for their delivery [37].

### Formative work that informed the intervention development

The design and adaptation of effective preventive interventions require community ownership, cultural flexibility, and fit with the delivery context to maximise effectiveness, appropriate training, and support to deliver, and relevance and acceptability to stakeholders [1, 29]. The intervention presented in this protocol is based on extensive formative work by the investigators. Firstly, this intervention is based on expertise in the use of CBT, programme development and evaluation, and experience of delivering preventive interventions in South African schools. Indeed, previous research by the investigators has demonstrated that existing evidence-based CBT-based activities and programmes can successfully be adapted to be culturally sensitive and to fit within the South African context [29–34, 38, 39]. Secondly, the intervention is informed by a systematic review by the investigators referred to earlier [36]. The findings of the review demonstrated that universal school-based approaches hold promise for reducing symptoms of anxiety and depression amongst CYP and are better delivered in group format and when based on principles of CBT. Thirdly, the intervention is informed by formative qualitative interviews conducted by the investigators with CYP (grades 5–7), school mental health counsellors, parents/caregivers, and teachers. These interviews elicited participant perspectives on what a universal school-based mental health intervention in this setting should look like and who should be involved [40]. Lastly, to adapt the intervention in the context of COVID-19, the intervention is informed by formative follow-up qualitative interviews with CYP (grades 5–7), school mental health counsellors, parents/caregivers, and teachers. These interviews asked participants about the challenges surrounding COVID-19 and various disease containment measures [41].

This formative work culminated in the manualised, psychoeducational CBT-informed intervention, *4 Steps To My Future* (4STMF). The four core steps of the programme are based on the principles of CBT and are designed to enhance self-esteem, promote helpful thinking, develop emotional regulation, and empower goal-focused action. Each of the four core steps is designed to be delivered over two brief school lessons lasting for 20–25 min per lesson (approximately 3–4 hours in total). Each lesson includes whole group and individual tasks. Whilst small group tasks were included in the original 4STMF, we had to adapt these in the light of COVID-19 so as to maintain safe social distancing. Further details on the programme content and activities are available from the authors on request. Participating children will be asked to complete tasks in between lessons to apply the skills learned in daily life. Classroom posters and some tangible materials (such as worksheets and notebooks) will provide personal reminders of the skills learned at each step. An informational handout will be sent to parents/caregivers after each step to inform them of the key learning points, what was done in the lessons, and how they can support this at home.

### Feasibility trial objectives

The primary objective of this study is to determine the acceptability and feasibility of the 4STMF programme. We will use a mixed methods design utilising quantitative and qualitative methods. We will determine acceptability and feasibility through assessing consent and assent rates, as well as session and programme completion rates. Fidelity checklists will be completed by the programme facilitators and independent observers for each lesson. These fidelity checks will elicit how confident, prepared, and enthusiastic facilitators appeared whilst delivering the programme, as well as how well they managed the classroom. Furthermore, the fidelity checklists will elicit how long it took to deliver a lesson, whether an activity was delivered or changed, and how confident, prepared, and enthusiastic the facilitators appeared during the delivery of that lesson. Furthermore, teachers will be asked to complete an evaluation form once the programme has been facilitated. Qualitative, semi-structured exit focus groups will be conducted with CYP following intervention delivery. We will determine the acceptability of our assessment measures (completion rates) and will explore pre- and post-intervention changes to determine sample size (power) for a future randomised controlled trial (RCT).

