### Characteristics of participants

Participants will be in grade 5 at participating schools (aged ~ 10–13 years). The intervention will be universally delivered, i.e. delivered to all participating children regardless of symptomatology or risk. Given the restrictions posed on this research by COVID-19 and given changes to school scheduling, we pragmatically decided to target the intervention at one grade, grade 5, only. There are approximately 20 eligible children per class with 6 and 8 classes at our target schools respectively. As such, whilst there are approximately 280 children eligible to take part in grade 5 across these 2 schools, we expect a sample of approximately 224 children to take part in this study which accounts for a 20% non-participation rate. We will calculate consent and retention rates at immediate post-intervention as well as 1-month follow-up. As per communication received from the Western Cape Education Department (WCED), no research may be conducted during the fourth term (October–December 2021) as schools are preparing and finalising syllabi for examinations. This could then mean that a 1-month follow-up assessment might not be possible with the children in the DIG.

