### Psychological well-being

We will undertake an exploratory analysis of our psychological measures. The purpose will be to (i) inform decision-making about which will be our primary outcome in a subsequent trial and (ii) to inform the power calculation for a subsequent RCT. The following standardised psychological measures will be completed at each assessment.

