### Randomisation and blinding

Two schools were randomly selected from a list of 21 schools within which the NGO operates. These two schools were then randomised to either immediate or delayed delivery of 4STMF. By the nature of the intervention, neither the participants nor the interventionists were blind to arm.

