#### Data analysis

Descriptive statistics will summarise our feasibility outcomes and demographic data. Quantitative data will be analysed using SPSS and other statistical software, as appropriate. Participant characteristics will contain both continuous and categorical variables. We will use means and standard deviations to summarise data collected on the continuous variables and frequencies and percentages to summarise data collected on the categorical variables. An exploratory analysis of the psychological outcomes will be undertaken. Analysis will involve pre- and post-comparisons within and between groups exploring baseline, post-intervention, and 1-month follow-up data.

Qualitative data will be transcribed verbatim and will be uploaded into ATLAS.ti 9 to be analysed deductively and/or inductively using both content analysis and thematic analysis [51]. Qualitative data will be focus group data collected from learners on completion of intervention delivery at both schools.

The findings obtained from our qualitative formative work were used to inform the development of the intervention material. Similarly, we will integrate both quantitative and qualitative data obtained from this feasibility and acceptability pilot study in our reporting of the main study outcomes. We will do so by providing descriptive data on our feasibility outcomes and complementing these numerical data with qualitative data obtained from our exit interviews. These exit interviews may then help us to understand qualitatively, for example, why the intended number of sessions was not completed.

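### The future RCT is to be sized from pre-post changes observed in a pilot with one school per arm, which is not a sound basis for a target difference

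*Protocol article*

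**What the plan says.** Under Feasibility trial objectives, the protocol article says the investigators "will explore pre- and post-intervention changes to determine sample size (power) for a future randomised controlled trial (RCT"). Under Psychological well-being it gives two purposes for the exploratory analysis of the scales: to "inform decision-making about which will be our primary outcome in a subsequent trial" and "to inform the power calculation for a subsequent RCT". The Data analysis section describes that analysis: "Analysis will involve pre- and post-comparisons within and between groups exploring baseline, post-intervention, and 1-month follow-up data".

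The design that produces these data has two clusters. Under Randomisation and blinding: "These two schools were then randomised to either immediate or delayed delivery of 4STMF". On numbers, Characteristics of participants says: "There are approximately 20 eligible children per class with 6 and 8 classes at our target schools respectively", and "we expect a sample of approximately 224 children to take part in this study which accounts for a 20% non-participation rate".

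The article names no target difference for the RCT and no source for an ICC. It does not say whether the RCT will randomise schools, classes or children.

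**The concern.** A sample-size calculation needs the difference worth detecting, plus nuisance quantities such as the SD, the baseline-to-follow-up correlation, attrition and the ICC. A pilot is a reasonable source for most of the second group and a poor source for the first. The objectives sentence makes the observed change the input, and the two comparisons planned under Data analysis each fail as a target difference:

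- **Within a school.** The change has no control. It mixes the programme's effect with maturation, repeat testing, the school calendar and COVID disruption.
- **Between schools.** Taking the difference in change removes a stable gap between the schools. It does not remove anything that happened at one school and not the other over the same weeks. With one school per arm, that is inseparable from the programme. For the same reason, between-school variance cannot be estimated.

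Informing the RCT's power is one of the two stated purposes of the psychological measures. An RCT sized on a change that happens to be too large would be underpowered. One sized on a change that happens to be too small would be wastefully large or might be abandoned.

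**Working it through.** **1. Pilot size.** 20 × (6 + 8) = 280 eligible, and 280 × 0.80 = 224 expected, which agrees with the article. If the 20% non-participation applies equally, the schools contribute 20 × 6 × 0.80 = 96 and 20 × 8 × 0.80 = 128.

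**2. Assumptions not in the document.** Two-sided alpha 0.05, planned power 80%, true effect d = 0.20 SD, and school ICC from 0 to 0.05.

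**3. Precision of the pilot's between-school difference (unadjusted, in SD units).** SE = √[2·ICC + (1 − ICC)(1/96 + 1/128)], where 1/96 + 1/128 = 0.01823. At ICC 0.02 this is √(0.04 + 0.98 × 0.01823) = √0.0579 = 0.241.

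**4. Consequence of an estimate one SE too high.** Per-arm size is n = 2(1.96 + 0.84)²/d² ≈ 15.70/d². For d = 0.20, n = 393. If the estimate is 0.20 + SE, then n = 15.70/(0.20 + SE)², and true power is Φ(0.20·√(n/2) − 1.96).

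| School ICC | SE | Estimate used | n per arm (393 needed) | True power |
|---|---|---|---|---|
| 0 | 0.135 | 0.335 | 140 | 39% |
| 0.01 | 0.195 | 0.395 | 101 | 29% |
| 0.02 | 0.241 | 0.441 | 81 | 25% |
| 0.05 | 0.343 | 0.543 | 54 | 18% |

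The n column is before any design effect. A design effect applied equally to the planned and the needed size cancels, so the power column stands.

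**5. How likely is serious mis-sizing?** Count an RCT as badly mis-sized in either of two cases:

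- True power is below 60%, meaning the estimate exceeds d × 2.80/2.21.
- The planned size is more than twice that needed, meaning the estimate is below d/√2. This includes an estimate of no benefit.

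With a normally distributed estimate, the chance is 68% at ICC 0 and 87% at ICC 0.05 for d = 0.20. It is 53% to 81% for d = 0.30, and 30% to 68% for d = 0.50.

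**6. Allowing for baseline.** With baseline adjustment, correlation 0.7 (assumed) and ICC 0, SE = √(0.51 × 0.01823) = 0.096. One SE too high then gives 179 per arm and true power of about 47%. The chance of serious mis-sizing falls to 56%, 39% and 15% for d = 0.20, 0.30 and 0.50. For a change score at ICC 0.02 with correlation 0.7 at both child and school level, SE = √(0.6 × 0.0579) = 0.186. That gives 106 per arm and about 31% power.

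**7. Within-school change.** Suppose d = 0.20 and untreated children would also improve by c. The expected within-school change is 0.20 + c, before any sampling error.

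- c = 0.1: n = 15.70/0.30² → 175 per arm, true power 46%.
- c = 0.2: n = 15.70/0.40² → 99 per arm, true power 29%.
- c = −0.1 (untreated children worsen): n = 15.70/0.10² → 1,570 per arm, four times the size needed.

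**The case against.** The strongest reply is that this is an exploratory aim in a condensed article on a feasibility pilot. The Psychological well-being section says only that the data will *inform* the power calculation, and nothing states that the mean change is the sole input. Exploring pre-post changes also yields the SD of change and the baseline correlation, which the RCT does need. Retention and completion rates are already planned. The smallest worthwhile difference and the ICC range belong to the RCT's own protocol.

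Much of that is fair, and it limits the point. It does not remove it. The objectives sentence says *determine*, names the change as the input, and is a positive statement rather than a detail left for later. The softer verb elsewhere does not correct it.

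A reader might also infer more than the document supports:

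- **That the primary outcome will be the scale that moved most.** The article states no such rule. It says the analysis will inform the choice, and it plans to judge the measures on completion rates. Selection bias from picking the largest change is possible but is not planned.
- **That the RCT will certainly be mis-sized.** The size of the error depends on effect, ICC and baseline correlation, none of which the article gives. With d = 0.50, ICC 0 and good baseline adjustment, the chance is only 15%.
- **That the RCT will randomise schools.** The article says only RCT. If classes were randomised, the class-level ICC would be the important one, and the pilot can estimate it.

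**Conclusion.** The point holds as a defect in one stated objective. Observed change from a pilot with one school per arm is not a sound target difference, whether taken within or between schools, and a school-level ICC cannot come from this design. The resulting RCT could be badly mis-sized. With an assumed true effect of 0.20 SD, one SE of upward error leaves true power between 39% (ICC 0) and 18% (ICC 0.05) on the unadjusted SE, or about 47% at ICC 0 with a baseline correlation of 0.7. For small true effects, serious mis-sizing is more likely than not. For larger ones it can be much less likely.

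This should be fixed rather than must be fixed. The primary objective is feasibility and acceptability, and those outcomes do not depend on the sentence.

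**What to change.** Reword the sentence in Feasibility trial objectives to say:

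- The observed pre-post change will not be used as the RCT's target difference. The target will be a pre-stated smallest worthwhile difference.
- The pilot will supply, for each scale, the SD, the baseline-to-follow-up correlation, and retention and completion rates, together with a class-level ICC and its confidence interval.
- If the RCT randomises schools, the school-level ICC will come from external data, and the RCT's size will be shown over a range of values (for example 0.01 to 0.05).

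As a safeguard, add to Psychological well-being that the primary outcome will be chosen on relevance, completion and measurement properties, not on size of change. This is a clarification, because the article states no contrary rule.

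The cost is a few sentences and some extra descriptive estimates from data already to be collected. The class-level ICC will be imprecise: with 14 classes of 16 children and a true value of 0.05 (assumed), its SE is about 0.04. It should be read as a range.

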## Methods/design

This paper reports on the protocol for the feasibility of a pilot intervention of the 4STMF programme in accordance with the Standard Protocol Items: Recommendations for Interventional Trials (SPIRIT) checklist (see Fig. 1).

**Fig. 1 Fig1:**
[figure not shown]
Standard Protocol Items: Recommendations for Clinical Trials (SPIRIT) figure—schedule of data collection

### Trial design

We will conduct a two-arm, randomised, feasibility pilot trial comparing immediate intervention group (IIG) delivery of 4STMF to a delayed intervention group (DIG). The consort diagram of the study design is shown in Fig. 2.

**Fig. 2 Fig2:**
[figure not shown]
Consort diagram of the study design for the 4STMF programme

